**Fig. 1 Fig1:**
[figure not shown]
Flow chart of the trial

**Table 1 Tab1:**
[figure not shown]
Schedule of enrolment, interventions, and assessments

**Table 2 Tab2:** The JOA [14] scoring system for assessment of low back pain. The score in a normal subject is the total of the best scores: (I+II+III+IV) = 29 points

Parameter	Finding	Score (points)
I. Subjective symptoms (9 points)		
a. Low back pain	None	3
	Occasional mild pain	2
	Frequent mild/occasional severe pain	1
	Frequent pain/continuous pain	0
b. Leg pain and/or tingling	None	3
	Occasional slight symptoms	2
	Frequent slight symptoms/occasional severe symptoms	1
	Frequent severe symptoms/continuous severe symptoms	0
c. Gait	Normal	3
	Able to walk > 500 meters although it results in pain tingling and/or muscle weakness	2
	Unable to walk > 500 meters owing to leg pain tingling and/or muscle weakness	1
	Unable to walk > 100 meters owing to leg pain tingling and/or muscle weakness	0
II. Clinical signs (6 points)		
a. Straight leg raising (includes a tight hamstring)	Normal (> 70°)	2
	30° to 70°	1
	< 30°	0
b. Sensory disturbance	None	2
	Slight disturbance (not subjective)	1
	Marked disturbance	0
c. Motor disturbance	Normal (Grade 5)	2
	Slight weakness (Grade 4)	1
	Marked weakness (Grades 0 to 3)	0
III. Restriction in activities (14 points)		
a. Turn over while lying	No restriction	2
	Moderate restriction	1
	Severe restriction	0
b. Standing	No restriction	2
	Moderate restriction	1
	Severe restriction	0
c. Washing	No restriction	2
	Moderate restriction	1
	Severe restriction	0
d. Leaning forward	No restriction	2
	Moderate restriction	1
	Severe restriction	0
e. Sitting about 1 h	No restriction	2
	Moderate restriction	1
	Severe restriction	0
f. Lifting or holding a heavy object	No restriction	2
	Moderate restriction	1
	Severe restriction	0
g. Walking	No restriction	2
	Moderate restriction	1
	Severe restriction	0
IV. Urinary bladder function (−6 points maximum)	Normal	0
	Mild dysuria	-3
	Severe dysuria	-6

**Fig. 2 Fig2:**
[figure not shown]
visual analogue scales(VAS) [15]

### Study population

The study population is the patients admitted to the orthopaedic ward and orthopaedic clinic of Wangjing Hospital, Chinese Academy of Traditional Chinese Medicine. The diagnostic, inclusion, exclusion, rejection, and termination criteria for this trial sample are as follows.

#### Diagnostic criteria

According to Kirkaldy-Willis’ statement of spinal instability [16], combined with the reports of many scholars [17–19], the clinical diagnostic criteria of DLI are as follows:(1) obvious and repeated low back pain, and severe pain or weakness; (2) local low back pain and/or pain associated with lower extremity involvement; (3) MRI, CT, and other examinations show obvious degeneration of lumbar disc and joint, which exclude other diseases; and (4) X-ray: (1) the leading edge of vertebral body showed distraction osteophyte formation or obvious stenosis of intervertebral space and (2) in the dynamic radiograph (hyperextension, hyperflexion lateral radiograph) of the lumbar spine, the slip between the adjacent two vertebrae was more than 3 mm (but the forward or backward slip of the upper vertebrae was not more than 1/4 of the sagittal diameter of the middle vertebrae, and the lesion was not more than 2 segments), or the angle between the adjacent vertebrae was more than 11°.

#### Inclusion criteria

(1) Diagnosed with DLI, (2) aged from 45 to 65 years old, and (3) provided informed consent.

#### Exclusion criteria

(1) Instability caused by congenital spinal diseases; (2) instability caused by spinal infection, traumatic fracture, tumor, tuberculosis, and osteoporosis; (3) with serious heart, cerebrovascular, hepatorenal and hematopoietic system and endocrine system diseases; (4) patients with mental illness or Alzheimer’s disease; (5) lumbar instability of dysplasia, isthmus, trauma, and pathology; and (6) severe skin injury or skin disease at the manipulation site

#### Rejection criteria

(1) The patients do not cooperate with the randomized program and do not receive treatment after randomization; (2) patients do not meet the inclusion criteria and/or exclusion criteria; (3) there is no treatment or any record of patients after enrollment; and (4) during the observation period, the patients received treatment by methods other than the protocol.

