## Method/design

### Study design

According to the random number table method [13], a total of 60 patients with DLI will be divided into sitting lumbar rotation manipulation group (the intervention group) and supine lumbar traction group (the control group), 30 cases in each group. DLI patients will be numbered according to the visit time, and any one number in the random number table will be selected as the starting point. A random number corresponding to each patient will be obtained along the same direction. Divide this number by 2, and the remainder of 0 will be the intervention group, and the remainder of 1 will be the control group. Two residents participating in this study will be responsible for generating the allocation order sequence.

The treatment of the two groups lasted for 3 weeks. The manipulation of the intervention group would be carried out once every other day, three times a week, a total of 9 times; the control group would be given lumbar traction once a day, five times a week, a total of 15 times. JOA [14] and VAS [15] scores will be recorded as the primary outcomes before the treatment and at the 1st, 3rd, 5th, 8th, 10th, 12th, 15th, 17th, and 19th days after the first treatment and follow-up visit at the 1st, 3rd, and 6th months. JOA [14] efficacy evaluation standard will be used to evaluate the overall efficacy as the secondary outcomes. When analyzing the results, the personnel who collect the data are blind to the grouping situation. The flow of this clinical trial is shown in Fig. 1; the schedule of enrolment, assessments, and interventions is presented in Table 1. JOA [14] and VAS [15] scores are presented in Table 2 and Fig. 2.

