#### Termination criteria

(1) Serious adverse events (life-threatening or affecting normal general work and life) occur; (2) in the course of treatment, the symptoms disappear completely and the patients are unwilling to receive treatment again; and (3) patients with severe and persistent anaphylaxis will stop treatment and be treated as invalid cases.

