### Sample size

As there is no literature reference to calculate the sample size of DLI treated by sitting lumbar rotation manipulation, and few clinical and statistical assumptions supporting the sample size calculations, so this study is an exploratory study. No references for the experience accumulation method indicated, so we selected 60 cases of small sample.

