### Statistical analysis

An independent statistician will use the SPSS V.25.0 software to perform the statistical analysis. Count data and grade data will be described by the number of case. The counting data will be tested by χ^2^; Wilcoxon rank-sum test will be applied to rank data. The measurement data will be statistically described with mean ± standard deviation. In group comparison, paired sample t-test will be applied. The rank sum test will be used for the difference comparison between groups. *P* < 0.05 will be considered statistically significant.

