## Discussion

Instability caused by lumbar degeneration is often seen in clinical diagnosis and treatment. Due to the narrowing of the intervertebral space, the lateral recess is relatively narrow. At the same time, the degeneration can cause the movement fulcrum of lumbar vertebrae to move back to the facet joint, making the facet joint degenerate and thicken, the facet joint subluxate, resulting in the narrowing of the lateral recess and spinal canal, the corresponding narrowing of the nerve root outlet, and stimulating the nerve root to produce back pain and other symptoms. These changes are aggravated during exercise, and symptoms such as low back pain and leg pain are aggravated when nerve roots are stimulated.

In order to ensure the effective and complete data, but also to protect the interests of the subjects, we will improve the compliance of the subjects from the following aspects. (a) When the subjects were screened, more telephone numbers of their family members were left to facilitate communication. During the experiment, all the questions will be answered in time, and the information will be collected and reported to the researchers. (b) Make the appointment of project examination, the preparation of application form and the record of data in advance to ensure that the subjects can enter the treatment course in time. Patiently explain the possible complications in the treatment, and tell the subjects not to be nervous once this happens, and the doctor will take necessary measures. (c) Humanistic care. During the manipulation, patients’ nervous mood will be appeased, and appropriate psychological comfort will be given, especially for older subjects. When it is time for treatment, telephone notice or SMS greetings will be given in advance. During the treatment, the patient’s condition will be continuously observed and reported to the researcher when necessary. At the same time, we will promote participant retention and compete follow-up in the above ways.

If the subjects could not complete the whole process of the trial due to any reasons, the reasons for their withdrawal should be recorded in detail. At the same time, attention should be paid to these patients for further observation and treatment within a certain period of time to protect the safety of patients after withdrawal from the trial. For the missing data processing, multiple imputation (MI) method [22] will be used to complete the missing data.

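### Rejection criteria 1, 3 and 4 appear to remove patients for events after randomisation or enrolment, which can bias the between-group comparison in a trial where doctors and patients know the arm

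*Protocol article*

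**What the plan says.** The Study population section of the protocol article presents the diagnostic, inclusion, exclusion, rejection and termination criteria together, as criteria for the trial sample. Eligibility has its own lists, so the rejection list is a further step. Its items are:

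- Item 1: "The patients do not cooperate with the randomized program and do not receive treatment after randomization".
- Item 2: patients found not to meet the eligibility criteria.
- Item 3: "there is no treatment or any record of patients after enrollment".
- Item 4: patients treated by methods outside the protocol during the observation period. Follow-up visits run to month 6.

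The Termination criteria section ends treatment for serious adverse events, for patients in whom "in the course of treatment, the symptoms disappear completely and the patients are unwilling to receive treatment again", and for severe anaphylaxis, where "patients with severe and persistent anaphylaxis will stop treatment and be treated as invalid cases".

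Three other places bear on the point. The Discussion says: "For the missing data processing, multiple imputation (MI) method [22] will be used to complete the missing data". The Intervention section lets usual care, including any medication, continue in both arms. The section on randomisation and blinding says that doctors and patients know which treatment is given, while the outcome evaluator and the statistician do not.

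**The concern.** Randomisation makes the two groups comparable only as long as the patients compared are those who were randomised. Items 1, 3 and 4 select on what happens afterwards. With doctors and patients unblinded, and 9 manipulation sessions in one arm against 15 traction sessions in the other, the chance of refusing the allocated treatment, leaving no record or seeking other care can differ by arm. It can also depend on how the patient is doing.

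Item 4 is the most serious. Patients who do badly over six months are the likeliest to look for other treatment, and the rule would then take their scores out. An arm that loses more of its poor responders looks better than it is.

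The objection is to a rule that the protocol states. It does not rest on the lack of a named analysis set, which could properly stand in a statistical analysis plan.

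**Working it through.** **Step 1: the texts side by side.**

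| Patient | Rejection criteria | Elsewhere in the article |
|---|---|---|
| No record after enrolment | Rejected (item 3) | Missing data completed by multiple imputation (Discussion) |
| Non-completer for any reason | Rejected if item 1, 3 or 4 applies | Reason recorded, further observation, imputation (Discussion) |
| Takes other treatment during follow-up | Rejected (item 4) | Usual care, including any medication, continues in both arms (Intervention) |

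A patient cannot be both rejected and imputed. In the last row, someone must judge which treatment counts as usual care and which as outside the protocol. The article does not say how, or that the judgement is made blind to arm.

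**Step 2: the plan's own figures.** The total of 60 was chosen without a calculation ("so we selected 60 cases of small sample"), with "30 cases in each group". The significance rule is P "< 0.05 will be considered statistically significant", taken here as two-sided. No effect size, SD, power or dropout rate is given, so there is no stated figure to reproduce. For scale, 30 per arm gives 80% power for a standardised difference of (1.960 + 0.842) × √(2/30) = 0.72 SD.

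**Step 3: size of the bias under assumed rejection.** Outcomes y are N(0,1) in both arms (higher is better), so there is no true effect. The chance of rejection is 1/(1 + exp(−(a − b·y))), where the slope b makes poor responders more likely to be rejected and a is set in each arm to give the chosen average rate. The mean of those retained is E[y(1−p)]/E[1−p]. With b = 1.5 it is 0.065 at 5% rejection, 0.122 at 10%, 0.175 at 15%, 0.277 at 25% and 0.327 at 30%. Type I error comes from 6,000 simulated trials per scenario (Monte Carlo standard error √(0.05 × 0.95/6000) ≈ 0.3 percentage points).

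| Rejected, arm A v arm B | Slope b | Spurious difference | Type I error |
|---|---|---|---|
| 10% v 10% | 1.5 | 0.122 − 0.122 = 0 | about 5% |
| 15% v 10% | 1.5 | 0.175 − 0.122 = 0.05 SD | about 5% to 5.5% |
| 10% v 5% | 1.5 | 0.122 − 0.065 = 0.06 SD | about 5.5% to 6% |
| 25% v 10% | 0.5 | 0.120 − 0.049 = 0.07 SD | about 5% to 6% |
| 25% v 10% | 1.5 | 0.277 − 0.122 = 0.16 SD | about 9% |
| 30% v 10% | 1.5 | 0.327 − 0.122 = 0.21 SD | about 11% to 12% |

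These are t-test results. With the rank sum test that the article names, the error is about 8.7% at 25% v 10% and 10.4% to 11.5% at 30% v 10% (slope 1.5). In patients, 25% v 10% of 30 is about 7.5 against 3.

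**Step 4: an upper illustration.** If the k worst outcomes of 30 are removed from one arm only (20,000 runs, rank sum test), the results are:

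- k = 2: 0.13 SD and about 8%.
- k = 3: 0.19 SD and about 10%.
- k = 6: 0.34 SD and about 24%.

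Removing the same numbers at random leaves the error at about 5%. The harm therefore needs removal that is related to outcome and differs by arm.

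**The case against.** The strongest case against is textual. The rejection list stands under the study population and not under the statistical analysis, and no sentence says that rejected patients leave the comparison. The Discussion plans imputation, which points towards keeping patients. This stands to the extent that exclusion from analysis is an inference. But rejection from the trial sample has no other evident meaning, and no sentence in the article keeps these patients in.

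Second, the numbers rest on assumed rates and an assumed slope. Under milder inputs the inflation is slight. An outcome slope also fits item 1 poorly, because refusal there comes before any response to treatment. Both points stand. The table is therefore a range of illustrations and predicts nothing for this trial.

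Third, keeping everyone is not a complete cure. A patient with no record after baseline has no score to analyse and depends on imputation. That stands too.

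Fourth, the article calls the study exploratory. That lowers the stakes, but it still states a hypothesis of benefit over traction and a 5% significance rule.

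A reader might also infer that the termination criteria remove patients according to outcome, so that symptom-free or harmed patients drop out of the data. The article does not support this. Those criteria end treatment; they do not say that assessment stops or that scores are discarded, and the Discussion provides for further observation. Nor can one say that a patient stopped for harm would be imputed from patients who did well: the imputation model is not described, and up to nine scheduled assessments during the treatment weeks may be available for that patient. What remains is an ambiguity. The anaphylaxis stop makes the patient an invalid case, and the Secondary outcomes section uses invalid for improvement below 25%. The term could mean counted as a non-response or discarded.

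**Conclusion.** The concern holds for rejection criteria 1, 3 and 4. Read with the Study population section, they appear to remove patients for events after randomisation or enrolment, in a design where those events can depend on arm and response. They also conflict with the article's own imputation plan and, for item 4, with continued usual care. Item 2 is less harmful if it is judged blind and on data from before randomisation.

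The size is not known. On the assumptions shown, bias runs from none (equal rates) through about 0.05 SD (15% v 10%) to about 0.16 SD with 9% type I error (25% v 10%). The last is roughly a fifth of the difference that 30 per arm can detect with 80% power (0.16/0.72 = 0.22).

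The point does not extend to the termination criteria as a source of exclusion. There the wording only needs clarifying.

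**What to change.** 1. Make the primary analysis all randomised patients in their allocated arm, using observed scores where they exist and the planned multiple imputation otherwise.
2. Use rejection items 1, 3 and 4 only to define a per-protocol set for a sensitivity analysis.
3. Reconcile item 4 with the statement that usual care, including medication, continues in both arms, and reconcile item 3 with the imputation plan.
4. Leave the treatment-stopping rules as they are. Add that JOA and VAS assessment continues to month 6 after treatment stops, and say whether an invalid case is counted as under 25% improvement or discarded.

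The cost is mainly wording, since the visits are already scheduled. There are two small downsides: non-adherence may dilute the estimate, and patients with no score after baseline will depend on the imputation.

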## Introduction

Degenerative lumbar instability (DLI) is a common disease that causes low back pain in clinic. It is difficult to completely recover from DLI, and it occurs repeatedly, which seriously affects the quality of life of patients. According to the data of the World Health Organization global disease burden research [1], among 301 diseases in 188 countries, low back pain ranks first in the disease burden indicators of developed and underdeveloped countries all the year round. In China, the disease burden caused by low back pain also ranks first. The epidemiological survey [2] shows that 20–30% of low back pain is related to lumbar instability, which shows that the disease brings huge economic and social burden.

The treatment of DLI includes non-surgical (conservative) treatment and surgical treatment. The choice of the two mainly depends on the degree of lumbar instability, the type of involved tissue, secondary deformity, the risk of complications, and psychological, social, economic and other comprehensive factors. Clinical conservative treatment of most patients with DLI can achieve good results [3, 4]. Absolutely lying in bed or strengthening the functional exercises of lumbar, back, and abdominal muscles can achieve the purpose of prevention and treatment of back pain. However, surgical treatment is limited to patients with obvious neurological symptoms, progressive aggravation of spondylolisthesis, and ineffective conservative treatment. It is generally believed that non-surgical treatment is the first choice for the treatment of DLI, such as bed rest, brace, manipulation, traction, physical therapy, and needle-knife.

The traditional Chinese manipulation has unique advantages in the treatment of lumbar and back pain, and the clinical reports [5–8] on the treatment of low back pain, lumbar disc herniation, lumbar facet joint disorder, lumbar spondylolisthesis, and other diseases with sitting rotation manipulation also show the effectiveness of this method.

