### Randomization, allocation concealment, and blinding

Upon completion of the baseline assessment, participants were randomly assigned by the physician to the sitting lumbar rotation manipulation group and the supine lumbar traction control group. Because doctors and patients are able to know which kind of intervention will be accepted, they cannot be blind to the treatment, but the result evaluator and data statistician are blind to the grouping and treatment.

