#### Lumbar traction in supine position control group

The operation of the lumbar traction in supine position [21] treatment method is as follows: the patient is in supine position with the chest band fixed in both armpits and the pelvic band fixed in the upper edge of the iliac crest. The tightness of binding is moderate. The traction weight starts from a small amount and increases to 50% of the patient’s weight. During traction, a triangular brace is placed in the lumbosacral part of the patient, which is located at the lower edge of the lumbar sliding instability segment. It will be taken once a day, 5 times a week, 30 min each time.

Implementing seated lumbar rotation manipulation and lumbar traction in the supine position group will not require alteration to usual care pathways (including use of any medication) and these will continue for both trial arms.

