### Outcome assessment

Variables for this clinical trial included the patient’s baseline, primary, and secondary outcomes.

The baseline will be completed before treatment, and the primary and secondary results will be measured at baseline and on the 1st, 3rd, 5th, 8th, 10th, 12th, 15th, 17th, and 19th days after the first treatment, and followed up at the 1st, 3rd, and 6th months. All primary and secondary outcomes will be evaluated by experienced doctors at Wangjing Hospital, and patient allocation results will be blind to them.

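### Rejection criterion 4 removes randomized patients for treatment they receive after randomization, which selects the JOA and VAS comparison on an event likely tied to poor response

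*Protocol article*

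**What the plan says.** The Study population section introduces five lists with the words "The diagnostic, inclusion, exclusion, rejection, and termination criteria for this trial sample are as follows". The Rejection criteria stand apart from the inclusion, exclusion and termination lists. Item 4 covers the case where "during the observation period, the patients received treatment by methods other than the protocol". Item 1 shows that the list reaches randomized patients: "The patients do not cooperate with the randomized program and do not receive treatment after randomization". Item 3 covers patients with no treatment or no record after enrolment.

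Other sections bear on the rule:
- **Timing.** Treatment lasts 3 weeks, and patients are then "followed up at the 1st, 3rd, and 6th months" (Outcome assessment). The article does not define the observation period.
- **Usual care.** In the section on the traction control group, the two treatments "will not require alteration to usual care pathways (including use of any medication) and these will continue for both trial arms".
- **Blinding.** Under Randomization, allocation concealment, and blinding: "doctors and patients are able to know which kind of intervention will be accepted, they cannot be blind to the treatment". The outcome evaluator and the statistician are blinded.
- **Missing data.** The Discussion says that "multiple imputation (MI) method [22] will be used to complete the missing data", directly after a passage on subjects who could not complete the trial.
- **Disease course.** The Introduction says of the condition: "It is difficult to completely recover from DLI, and it occurs repeatedly".

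**The concern.** Randomization makes the two groups comparable at baseline. Dropping patients for something that happens later keeps that comparability only if the event is unrelated to outcome in both arms, or if it selects equally in both. Outside treatment for back pain is unlikely to be unrelated to outcome: the patient who is not improving, or who relapses, is the one likely to look elsewhere. This is a clinical inference, which the article does not state.

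The exposure may be long. If the observation period includes follow-up, a patient who completes all 3 weeks of treatment and seeks other care for a relapse at month 4 is rejected.

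The bias can go either way. If one arm loses more poor responders for reasons other than efficacy, for instance because unblinded patients in that arm look elsewhere more readily, that arm looks better than it is. If the rule works identically in both arms and manipulation is truly better, more control patients are removed and the real effect is understated.

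A lesser point is where the rule's boundary lies. Continued usual care can be read as exempt, but the line for non-drug care is unclear, and staff who know the allocation could draw it differently by arm.

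**Working it through.** **Does rejection mean removal?** The article states no consequence, so this rests on reading the sections together.
- Item 4 sits beside patients never treated and patients with no record, who are grounds for dropping a case.
- Stopping treatment has its own list, the Termination criteria. There, patients with severe anaphylaxis are classed as invalid, which is the failure category of the secondary outcome, so they appear to be counted. Rejection must do something else.
- Imputation fills missing values. A patient who took other treatment and still attended visits has none.

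Removal is therefore the natural reading, though not a certain one.

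**How large could the effect be?** The plan gives no rejection rate, effect size or SD, so it has no figure to reproduce.

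Inputs from the article: 30 per arm (Study design); a rank-sum test between groups at 0.05 (Statistical analysis), taken as two-sided. All rates, correlations and effects below are assumptions.

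Model: outcome Y has SD 1, and higher is better. A patient is rejected when U = −ρY + √(1−ρ²)Z exceeds a cut-off c, where Z is independent standard normal noise. The correlation ρ runs from 0 (rejection unrelated to outcome) to 1 (fully determined by it). With λ(c) = φ(c)/Φ(c), the mean outcome of those kept in an arm with true mean 0 is ρλ(c).

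*1. No true effect, different rejection rates.* Bias = ρ[λ(c_a) − λ(c_b)], in favour of arm a, which loses more. The values of λ are 0.424, 0.350, 0.274 and 0.195 at 25%, 20%, 15% and 10% rejected.

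| Rejected | Bias (SD) | ρ = 0.5 | ρ = 1 |
|---|---|---|---|
| 25% v 10% | (0.424 − 0.195)ρ = 0.229ρ | 0.114 | 0.229 |
| 20% v 10% | (0.350 − 0.195)ρ = 0.155ρ | 0.078 | 0.155 |
| 15% v 10% | (0.274 − 0.195)ρ = 0.079ρ | 0.040 | 0.079 |
| 15% v 15% | 0 | 0 | 0 |

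For 25% v 10%, simulated type I error (20,000 trials) is 4.7%, 6.7% and 16.0% at ρ = 0, 0.5 and 1.

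*2. Same cut-off in both arms, true effect d.* Estimate = d + ρ[λ(c + ρd) − λ(c)]. Take d = 0.5 and 20% of controls rejected, so c = 0.842.
- ρ = 0.5: 0.5 + 0.5 × (0.255 − 0.350) = 0.45.
- ρ = 1: 0.5 + (0.178 − 0.350) = 0.33.

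| ρ | Manipulation arm rejected | Estimate (SD) | Power |
|---|---|---|---|
| 0 | 20.0% | 0.50 | 37% |
| 0.5 | 13.7% | 0.45 | 35% |
| 1 | 9.0% | 0.33 | 28% |

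Power with all 60 kept is 45% (10,000 trials per figure).

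*3. Would imputation repair it?* Suppose rejected patients were imputed arm by arm, by regression on one earlier visit that correlates r with the outcome. In case 1 at 25% v 10% and ρ = 0.5, the bias of 0.11 SD falls to 0.11, 0.09 and 0.06 SD at r = 0.3, 0.5 and 0.7. At ρ = 1, the 0.23 SD falls to 0.22, 0.20 and 0.16 SD. Imputation from the earlier visit removes only part of it, because rejection depends on the outcome itself.

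**The case against.** The strongest objection is that the harm depends on a step the article never states. Analysis populations are commonly defined in a full protocol or SAP that is not shown here, and the phrase about the trial sample introduces the termination list as well. The Discussion's missing-data text covers subjects who fail to complete the trial whatever the reason, which could be read to include rejected patients. This stands as a reason to word the point conditionally. It does not remove the point, because the rule itself is stated, and no section clearly keeps these patients in.

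Second, the trigger may be narrow. Medication continues as usual care, so analgesics, an obvious rescue, need not trigger rejection, and the relapse argument needs an observation period that covers follow-up. Nor does the article say who applies criterion 4. All of this is fair, and it makes the assumed 25% v 10% an illustration rather than a forecast.

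Third, the size is modest under middling assumptions: 0.11 SD and a type I error near 7% at ρ = 0.5. The 16% figure needs outside treatment to be determined wholly by outcome. Most of the power loss at ρ = 0.5 comes from lost patients, since ρ = 0 already gives 37% and selection takes off about 2 points more. The trial also calls itself exploratory. This stands too, and it limits how serious the point is.

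**Conclusion.** The concern holds, as something that should be fixed. Criterion 4 is a written rule that takes out randomized patients for a later event likely to follow poor response.

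Under the assumed rates, the bias with no true effect runs from zero (equal rates, or rejection unrelated to outcome) to 0.23 SD at 25% v 10%. With a true 0.5 SD effect and one rule for both arms, the estimate lies between 0.50 and 0.33 SD. Even where there is no bias, losing 20% per arm takes power from 45% to 37%.

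These sizes rest on three conditions the article does not settle: that rejected patients leave the comparison, that the trigger is broad enough to matter, and that outside treatment tracks outcome. The direction of the bias cannot be fixed in advance. The unclear boundary of usual care is secondary.

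**What to change.** Make these changes:
- State that all randomized patients stay in the primary JOA and VAS comparison, in the arm to which they were allocated, whatever other treatment they receive.
- Go on collecting their scores after any such treatment, through month 6.
- Use criterion 4 only to define a per-protocol sensitivity set.
- State that usual care continued in both arms is not a ground for rejection, and tabulate co-treatment by arm.

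With everyone kept, the usual-care boundary affects only the sensitivity set. If the sponsor already meant to analyse everyone, the same sentences remove the contrary reading.

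The cost is two or three sentences and one table. The downside is that the estimate then reflects manipulation or traction on top of whatever other care was used. If co-treatment helped by 0.5 SD and were used by 25% v 10%, it would add (0.25 − 0.10) × 0.5 = 0.075 SD to the arm that used it more. The co-treatment table lets readers judge this.
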